### Imaging Data Analysis

#### GABA Spectroscopy

Data processing for the GABA quantification is carried out using Gannet v. 3.1.5, an open-source software coded with MatLab (52). Ratios of GABA levels between the affected and unaffected hemispheres, before and after suprasensory or subsensory RPSS, will be compared (53) in the EARLY and the CHRONIC groups. The pipeline for analysis is shown in Supplementary Materials.

##### pCASL Data

Post-processing of pCASL data is performed offline using a Java-based software package called CereFlow (Translational MRI, LLC, Los Angeles, CA, USA). First, label and control paired ASL images are corrected for motion and physiological noise using principal component analysis (54). Subsequently, pairwise subtraction between label and control images is performed, averaging to generate the mean difference dataset. CBF is then calculated using the standard pCASL model recommended by ASL white paper (55). The computed CBF maps are then normalized into a canonical space of the Montreal Neurological Institute template. Once normalized, an additional template of cerebral vascular territories is applied to extract the average CBF values in the following regions: leptomeningeal and perforating anterior cerebral artery, leptomeningeal and perforating middle cerebral artery, posterior cerebral artery, anterior choroidal artery, and posterior communicating artery on both (56). Furthermore, the Alberta Stroke Program Early CT Score system is applied to extract average CBF and arterial transit time (ATT) values in M1—M6 perfusion territories, the caudate nucleus, the lentiform nucleus, and the internal capsule (57, 58).

##### FMRI Pre-processing

The FMRI data processing is performed using FMRI Expert Analysis Tool (FEAT) Version 6.00 in FSL^1^ High-resolution registration to the MNI152 standard space image is carried out using FLIRT (59, 60). To properly register patient's brain images into standard space, we use spatial normalization using cost function masking (61), first registering functional images into patients' T1 images, and then to MNI 152 standard space using a lesion mask to down-weight affected tissue during the registration process. Lesion masks will be hand-drawn by a researcher who received extensive training in how to perform this procedure. The following pre-statistics processing is applied: motion correction using MCFLIRT (60), slice-timing correction using Fourier-space time-series phase-shifting, non-brain tissue removal using BET (62), spatial smoothing using a Gaussian kernel of FWHM 5 mm, grand-mean intensity normalization of the entire 4D dataset by a single multiplicative factor, and high-pass temporal filtering (Gaussian-weighted least-squares straight line fitting, with sigma = 120 s). Time-series statistical analysis is carried out using FILM with local autocorrelation correction (62).

#### Sample Size

Considering the SD of the data from Conforto et al. (22), it was estimated that to assess the primary outcome with a power of 80%, 68 patients should be included in the protocol. Considering an expected 5% dropout rate, the sample size was increased to 72. Half of the patients will have <6 months post-stroke and half, at least 6 months. Forty-eight patients will be included at HIAE or HCFMUSP and 24 at HSR.

### Statistical Analysis

Mean (±SD) or median (ranges) is presented according to the data distribution. Normality is tested with the Shapiro–Wilk test. Changes in JTT scores, strength, GABA levels, and CBF are compared between the four groups with general linear models or generalized estimating equation models with factors INTERVENTION (suprasensory/subsensory) and GROUP (subacute/chronic) according to the distribution of the data. The *p*-values below 0.05 are considered statistically significant.

For perfusion analyses, ratios between CBF in the affected/unaffected hemisphere and ratios between CBF in each region of interest in the affected/unaffected hemisphere are assessed. Due to the exploratory nature of these analyses, corrections for multiple comparisons are not performed.

For fMRI, a statistical analysis is implemented using a general linear model approach. Activity in ipsilesional and contralesional M1 during finger tapping is modeled by 30 s boxcar convolved with a double gamma function regressor. We also include a regressor with the first temporal derivative of the main regressor and nuisance regressors derived from the extended motion parameters. Two first-level analyses per participant are run, one pre-stimulation and one post-stimulation. Second level of analysis is carried to estimate the within-subject contrast between pre- and post-stimulation using a fixed-effects model, by forcing the random effects to zero in FLAME (FMRIB's Local Analysis of Mixed Effects) (63–65). At the third level of analysis, we estimate contrasts for each group of participants using one-sample *t*-tests to verify if there were effects of stimulation and independent *t*-tests to see changes between groups using a mixed effects model in FLAME (FMRIB's Local Analysis of Mixed Effects) stage 1 (63–65). Z (Gaussianized T/F) statistic images are thresholded using clusters determined by *Z* > 3.1 and a corrected cluster significance threshold of *p* = 0.05 (66). If there is a significant difference in change in motor performance (JTT or strength) between suprasensory and subsensory groups in either the chronic or subacute stage after stroke, bivariate analyses are performed (regressions or chi-square tests) to assess the relationship between each of these variables at baseline, and the magnitude of the improvement in behavior: baseline JTT or strength, age, sex, the intensity of RPSS (relative to sensory threshold), extent of BOLD activation (number of voxels and signal intensity) in M1, CBF (global and regional), or GABA concentration in M1 at baseline. Multiple regression is performed to assess the effects of variables if *p*-values are below 0.1 in bivariate analyses 0.05 (66).

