**Methods:**

In this multicenter, randomized, parallel-group, proof-of-principle clinical trial with blinded assessment of outcomes, we compare the effects of one session of suprasensory or subsensory RPSS in patients with ischemic or hemorrhagic stroke and upper limb paresis. Clinical assessment and MRI will be performed only once in each subject (either at an early or at a chronic stage). The primary outcome is the change in performance in the Jebsen–Taylor test. Secondary outcomes: hand strength, cerebral blood flow assessed with arterial spin labeling, changes in the blood oxygenation level-dependent (BOLD) effect in ipsilesional and contralesional primary motor cortex (M1) on the left and the right hemispheres assessed with functional MRI (fMRI) during a finger-tapping task performed with the paretic hand, and changes in GABA levels in ipsilesional and contralesional M1 evaluated with spectroscopy. The changes in outcomes will be compared in four groups: suprasensory, early; subsensory, early; suprasensory, chronic; and subsensory, chronic.

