Since excitability changes over time after lesion onset, and effects of neuromodulation interventions are known to be state-dependent (19), it is expected that results of these interventions vary at different stages after stroke. It is possible that, early after lesion onset, the variability in activity or excitability during the dynamic process of spontaneous recovery contributes to a less consistent effect of neuromodulation interventions. A systematic review and meta-analysis indicated that the potential benefits of transcranial direct current stimulation might be greater in patients in the chronic than in the subacute stage after stroke (26, 27). Furthermore, constraint-induced movement therapy (CIMT), a rehabilitation intervention that increases afferent input and provides training to decrease learned non-use of the upper limb, seems to be more beneficial in the chronic than in the subacute phase after stroke considering that the EXCITE trial (28) showed significant benefits of CIMT in patients treated between 3 and 9 months post-stroke, whereas the VECTORS (29) study showed no differences in effects of this intervention, compared to usual care, on average within the first 10 days after stroke.

Data from TMS studies suggest that RPSS enhances cortical excitability in animals (30), healthy subjects (31, 32), and patients in the chronic phase after stroke affecting the corticospinal tract (24). RPSS, compared to no stimulation (sham), leads to an increase in signal intensity and in the number of voxels activated in the primary motor cortex (M1) during thumb movements, in a paradigm of functional MRI (fMRI) based on the blood oxygen level-dependent (BOLD) effect. Perfusion in M1 assessed with arterial spin labeling at rest in healthy subjects increases after RPSS (7). This finding may be explained by increased blood flow driven by enhanced neuronal activity in M1. Whether RPSS can increase BOLD activation or global/regional cerebral blood flow (CBF) in subjects with stroke at different stages remains to be determined.

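### GABA and CBF are described as affected/unaffected ratios, which hide two-sided change and the side that changed, and no primary motor cortex region is listed for CBF

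*Protocol article*

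**What the plan says.** The abstract's Methods paragraph lists, among the secondary outcomes, "changes in GABA levels in ipsilesional and contralesional M1 evaluated with spectroscopy". It lists CBF by arterial spin labeling separately, with no region attached. The Introduction repeats the two-sided GABA target. It motivates the perfusion measurement by a reported rise in primary motor cortex perfusion in healthy subjects after stimulation, and then states the open question: "Whether RPSS can increase BOLD activation or global/regional cerebral blood flow (CBF) in subjects with stroke at different stages remains to be determined".

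The analysis variables are described in three places:

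- GABA Spectroscopy: "Ratios of GABA levels between the affected and unaffected hemispheres, before and after suprasensory or subsensory RPSS, will be compared".
- Statistical Analysis, general model sentence: "Changes in JTT scores, strength, GABA levels, and CBF are compared between the four groups". No ratio is mentioned.
- Statistical Analysis, perfusion paragraph: "ratios between CBF in the affected/unaffected hemisphere and ratios between CBF in each region of interest in the affected/unaffected hemisphere are assessed".

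The pCASL Data section gives the CBF regions in two sets. In the first, "an additional template of cerebral vascular territories is applied to extract the average CBF values in the following regions", followed by a list of arterial territories. The second set, from the Alberta Stroke Program Early CT Score, gives "values in M1—M6 perfusion territories, the caudate nucleus, the lentiform nucleus, and the internal capsule". Neither set contains the primary motor cortex or the precentral gyrus.

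**The concern.** The stated targets are the level in each motor cortex (GABA) and global or regional flow (CBF). The variable described in most detail is a quotient of the two sides. Two-sided effects are plausible here, since the plan itself treats the contralesional motor cortex as a place where change may occur. If stimulation moves both sides together, the quotient stays flat and a real effect is reported as none. If only the contralesional side moves, the quotient changes just as it would for an opposite ipsilesional effect. A trial that wants preliminary evidence on mechanism needs to tell these cases apart.

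CBF has a second problem. Its rationale concerns the primary motor cortex, but the values to be extracted are averages over larger or different regions. The label M1 also carries two meanings in the article: primary motor cortex in the abstract and Introduction, and a perfusion territory in the pCASL Data section. A result reported for M1 perfusion could be taken for the one that the rationale is about.

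**Working it through.** The plan gives no figure to reproduce on this point. The check is algebra on the ratio plus a comparison of the sections. All percentage changes below are illustrative assumptions, not values from the article.

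**1. What the ratio retains.** Let *a* and *u* be the proportional changes after stimulation on the affected and unaffected sides. The proportional change in the affected/unaffected ratio is

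(1 + a)/(1 + u) - 1,

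which does not depend on the baseline levels.

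| Affected | Unaffected | Calculation | Ratio change |
|---|---|---|---|
| +10% | +10% | 1.10/1.10 - 1 | 0.0% |
| -10% | -10% | 0.90/0.90 - 1 | 0.0% |
| +10% | +5% | 1.10/1.05 - 1 | +4.8% |
| +10% | 0% | 1.10/1.00 - 1 | +10.0% |
| 0% | -10% | 1.00/0.90 - 1 | +11.1% |
| 0% | +10% | 1.00/1.10 - 1 | -9.1% |

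An equal two-sided change vanishes, and a partly two-sided change shrinks. A one-sided change is kept in full, but rows four and five show that the ratio cannot say which side produced it. The same holds for comparisons between the four groups: if one arm changed equally on both sides and another did not change at all, their ratio changes would both be zero.

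**2. Dilution of a motor cortex CBF change.** Suppose that flow rises by 10% in primary motor cortex only, that baseline flow is uniform, and that motor cortex makes up a share *f* of the territory averaged. The territory then rises by f × 10%:

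- f = 5%: 0.5%
- f = 10%: 1%
- f = 20%: 2%
- f = 50%: 5%

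The article does not give the shares, so this is a range. The change is diluted but not absent.

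**3. Noise, the argument for a ratio.** If log changes on the two sides have equal variance and correlation ρ, the SD of the log-ratio change divided by that of a single-side change is √(2(1 - ρ)). This is 1.41 at ρ = 0, 1.00 at 0.5, 0.63 at 0.8 and 0.45 at 0.9. The ratio is the quieter measure only when ρ exceeds 0.5. The article gives no ρ.

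**4. Sections side by side.** For GABA, the abstract and the general model sentence name levels, while the GABA Spectroscopy section names ratios. For CBF, the general model sentence names changes in CBF and the next paragraph names only ratios. Nothing says whether the ratios replace the levels or supplement them. Global CBF appears again only as a baseline predictor, in an analysis that runs only if behaviour differs between the stimulation arms. That is not an analysis of CBF change.

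**The case against.** A reader might infer that the imaging analysis as a whole cannot show a motor cortex change. The article does not support that. BOLD activity is modelled in both motor cortices without a ratio. The spectroscopy voxel is centred on the hand knob in each hemisphere, so the GABA ratio is itself a motor cortex measure and shows a one-sided change in full.

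Nor is a global CBF change hypothesised. The stated imaging hypothesis is that changes are greater in the chronic than in the early stage; global flow is posed as an open question. The abstract does not tie the CBF outcome to the motor cortex, so territorial CBF does not contradict that outcome. It is a poor fit to the rationale. It would also be wrong to say that motor cortex CBF is not measured: CBF maps are computed and normalised to a standard template, so only the extraction is missing.

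A reader might add a multiplicity complaint about the many regional ratios. The perfusion analyses are openly called exploratory and uncorrected, and the regions overlap, so a false-positive figure that assumes independent tests would not be meaningful.

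The general model sentence can be read as comparing non-ratio changes, with the ratios as an addition. That reading is possible, and it would meet part of the concern. It is not stated, and it would still supply no motor cortex region for CBF. Scaling to the other hemisphere can also reduce noise, which is a fair reason to keep the ratio but not to make it the only measure.

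**Conclusion.** The point holds in a limited form. As described, the GABA and CBF ratios cannot show change common to both hemispheres and cannot attribute a change to one side. This does not match the GABA outcome of change in each motor cortex, the changes named in the general model sentence, or the global and regional CBF question. Separately, no primary motor cortex region is listed for CBF although motor cortex perfusion is the rationale, so a focal effect would be diluted.

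The cancellation is exact algebra. How much it matters depends on how two-sided the true effects are, which is unknown. The dilution figures rest on assumed shares and uniform baseline flow. The consequence is confined to secondary outcomes, with the perfusion analyses declared exploratory; the primary outcome is untouched. This is a worthwhile, inexpensive improvement and not a flaw that threatens the trial.

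**What to change.** - State that change after stimulation is analysed separately for the ipsilesional and contralesional side, for both GABA and CBF, for example as log change. Use this wording consistently in the GABA Spectroscopy and Statistical Analysis sections.
- Add change in whole-brain CBF.
- Add a hand-knob primary motor cortex CBF region in each hemisphere, matching the spectroscopy target, extracted from the existing CBF maps.
- Keep the affected/unaffected ratios and the other territories as supportive analyses.
- Label the Alberta sectors so that their M1 cannot be read as primary motor cortex.

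The cost is re-extraction from maps already produced and some rewording; no new scans or patients are needed. The downside is that single-hemisphere CBF can be noisier than a ratio when the two sides fluctuate together, so both should be reported.

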### Randomization, Allocation Concealment, and Blinding

Patients are randomized to one of four groups: suprasensory or subsensory in the EARLYgroup, suprasensory or subsensory in the CHRONICgroup. The randomization sequence was created by a statistician in an Excel spreadsheet in 12 blocks of 4 patients at HIAE or HCFMUSP and in 6 blocks of 4 patients at HSR, weighted 1:1 toward the suprasensory treatment group. Randomization was stratified by phase after stroke (subacute or chronic), gender, age (18–50, 51–79, ≥80 years), side of upper limb paresis and baseline upper limb FMA scores (≤47/66 or >47/66). Randomization tables are kept in locked cabinets accessed only by the principal investigator and the researcher responsible for RPSS in each center, and password-protected files.

Researchers responsible for the evaluation of outcomes are blinded to treatment allocation. All researchers received training before the onset of data collection. Videos with instructions for administration of the JTT were produced, and realistic simulations were performed. Patients are not informed about the type of stimulation they receive (suprasensory or subsensory) and are naive to the experimental hypothesis. They are instructed not to share their perceptions about the experimental sessions with other participants and researchers.

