During fMRI scans, six blocks of finger tapping followed by rest are performed. Before being scanned, subjects practice a self-paced rhythmic finger tapping task consisting of 6 epochs of 30 s of finger tapping alternated with epochs of 30 s rest. Patients are instructed to keep their eyes open. Performance of finger tapping is not one of the inclusion criteria but because patients must be able to perform the JTT in order to be included, only patients with mild upper limb impairments participate in the study. All patients are encouraged to try to perform the task as accurately as possible. It is possible that some patients, despite mild motor impairments, are not able to accurately perform finger tapping. In order to check task performance, finger tapping during fMRI is videotaped. Two researchers review all the videos. Data from patients unable to perform finger tapping are excluded from the analysis.

Sleepiness can potentially influence task performance and GABA levels. Subjects are instructed not to drink alcohol 48 h before the tests, sleep the night before, drink the usual amount of coffee, and do not perform vigorous physical activity on the day of the test. Before MRI (Figure 1), the Epworth Sleepiness Scale is evaluated (50). VAS scores for sleepiness, fatigue, and anxiety (51), blood pressure, and heart rate are assessed before and after MRI.

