Another potential limitation of this study is the choice of the control stimulation. There is no consensus about the best control or sham condition for RPSS. According to a standard definition, “sham is an arm type in which a group of participants receives a procedure or device that appears to be the same as the actual procedure or device being studied but does not contain active processes or components”^2^ We opted for subsensory stimulation—the stimulator is on, but subjects do not have paresthesia. Other possible controls are no stimulation (with or without placement of electrodes on the skin) or leg stimulation (11, 12, 14). A disadvantage of no stimulation is that subjects may conclude that they are not receiving active treatment, to the lack of paresthesia at any point during the experiment. A limitation of subsensory stimulation is that, in the 1st weeks after stroke (44), this intervention may have similar effects to stimulation above sensory threshold in the chronic phase. A caveat of stimulation of lower limb nerves is that subjects may deduct that this consists of a control/sham intervention if the upper limb performance is tested, or if the upper limb training is provided as part of the experimental protocol. Further studies are necessary to compare patients' perceptions about different types of controls for RPSS.

In summary, the results of the protocol “Comparison between the mechanisms underlying the effects of peripheral repetitive stimulation on upper limb motor performance in the subacute and chronic phases after stroke” will be relevant to inform future clinical trials in order to tailor RPSS to patients more likely to benefit from this intervention, in early or chronic stages. In addition, this study will provide preliminary data about mechanisms underlying effects of this intervention on GABA levels in the primary motor cortex, BOLD activation, and CBF perfusion in different stages after stroke.

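### The third-level fMRI analysis assigns the verification of stimulation effects to within-group one-sample t-tests of pre-to-post BOLD change, which cannot separate stimulation from time; the randomised contrast should have that job

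*Protocol article*

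**What the plan says.** The fMRI paragraph of Statistical Analysis has three levels. The first models each scan separately. The second is used to "estimate the within-subject contrast between pre- and post-stimulation using a fixed-effects model". The third has two parts. The first part works group by group: "we estimate contrasts for each group of participants using one-sample" t-tests of that contrast. The purpose which the article attaches to this part is worded as "tests to verify if there were effects of stimulation". The second part consists of t-tests for independent samples, and its purpose is worded differently, as "tests to see changes between groups using a mixed effects model in FLAME". Maps are thresholded at cluster-forming Z > 3.1 with "a corrected cluster significance threshold of" p = 0.05.

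The randomised groups are "suprasensory or subsensory in the EARLYgroup, suprasensory or subsensory in the CHRONICgroup". The Discussion treats subsensory stimulation as the control ("Another potential limitation of this study is the choice of the control stimulation").

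For the Jebsen–Taylor test (JTT), strength, GABA and cerebral blood flow, the same section specifies models with an intervention factor and a phase factor. BOLD is not in that list, and the fMRI paragraph names no suprasensory-versus-subsensory contrast.

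**The concern.** The question attached to the one-sample test is whether stimulation had an effect. The hypothesis it tests is that mean activation is the same at two scans separated by a 2-hour session. These coincide only if nothing else changes activation between the scans.

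The protocol itself describes things that might. Under Imaging Outcomes, "subjects practice a self-paced rhythmic finger tapping task consisting of 6 epochs of 30 s of finger tapping" alternating with rest before scanning, and tapping is then performed in both scans. Between the scans, patients sit for 2 hours watching videos (Interventions). Imaging Outcomes also says that sleepiness can influence task performance, and has sleepiness, fatigue and anxiety scored before and after MRI.

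A significant one-sample map, or one that is significant in one arm and not in the other, could then be taken as evidence that stimulation altered motor cortex activation when the randomised comparison shows no difference. This matters for the mechanistic conclusion: the Discussion says that a relation between BOLD activation and responsiveness should inform patient selection in later trials.

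**Working it through.** **Plan's own figure.** The protocol gives no sample size or power for fMRI, so there is none to reproduce. Its only related figure, 68 patients raised to 72 for 5% dropout, checks (68/0.95 = 71.6, rounded up to 72) but does not bear on this point.

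**Which test is free of a common time effect.** Let the mean pre-to-post contrast in an arm be τ + δ, where τ is change from any cause other than stimulation and δ is the stimulation effect.
- One-sample test in one arm: H0 is τ + δ = 0. With δ = 0 it rejects too often whenever τ ≠ 0.
- Between-arm test within a phase: (τ + δ_supra) − (τ + δ_sub) = δ_supra − δ_sub. A τ shared by the arms cancels, and randomisation is what justifies treating it as shared.
- Intervention-by-phase contrast: (δ_supra − δ_sub) in chronic minus the same in early. τ cancels within each phase, even if it differs between phases.
- Early versus chronic within one arm would not isolate stimulation, because τ may differ by phase. So it matters which pair the independent t-tests compare.

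**Inputs for an illustration.**
- Imaged patients: imaging is at HIAE (Imaging Outcomes). HIAE and HCFMUSP together contribute 48 (Sample Size). If all 48 were imaged and split evenly, n = 48/4 = 12 per group. This is a ceiling, because 48 is not HIAE alone, MRI contraindications apply, and patients unable to tap are excluded. n = 8 is taken as a lower illustration. Eighteen per group would need all 72 imaged, which imaging at HIAE rules out.
- Time effect d = τ / SD of the within-patient contrast. The documents give no value; 0.3 to 0.8 is assumed.
- δ = 0 in every group.

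**Region level, uncorrected two-sided alpha 0.05.** The rejection rate is P(|T| > t_crit), with T noncentral t on n − 1 degrees of freedom and noncentrality d√n. At d = 0.5:
- n = 8: t_crit = 2.365, noncentrality 0.5 × √8 = 1.414, rate 0.23.
- n = 12: t_crit = 2.201, noncentrality 0.5 × √12 = 1.732, rate 0.35.

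| d | n = 8 | n = 12 | between-arm test |
|---|---|---|---|
| 0 | 5% | 5% | 5% |
| 0.3 | 11% | 16% | 5% |
| 0.5 | 23% | 35% | 5% |
| 0.8 | 50% | 71% | 5% |

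Simulation with 100,000 runs at d = 0.5 gave 0.23 and 0.36 for the one-sample test, and 0.050 at both sizes for the between-arm test.

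Exactly one of the two arms within a phase is positive with probability 2p(1 − p). At n = 12 and d = 0.5 this is 2 × 0.353 × 0.647 = 0.46.

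**Single voxel at Z > 3.1, one-sided.** The nominal rate is 0.1%. At d = 0.5 it becomes 1.8% (n = 8) and 4.4% (n = 12). The stricter threshold lowers the rate but does not remove the bias. Cluster-level rates depend on the spatial extent of the time effect and on smoothness, and were not computed.

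**The case against.** The strongest reply is that the controlled comparison is already planned. The same sentence specifies independent t-tests on the same contrast in a mixed-effects model, the Abstract says changes in outcomes will be compared across four groups, and the Introduction's imaging hypothesis is a between-group one. This stands: it would be wrong to infer that the plan has no between-group test for BOLD. What remains is that the article assigns the two tests different questions, gives the stimulation question to the uncontrolled one, and leaves the pairs unnamed. The assignment is stated wording, not detail deferred to another document.

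Second, a reader might infer that every practice or time effect will be reported as a stimulation effect. The documents do not support that. An effect must pass the cluster threshold, no reporting rule is stated, and the Discussion calls the mechanistic evidence preliminary.

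Third, some sources of change are mitigated. Practice before the first scan should reduce novelty, patients are questioned every 5 minutes during stimulation, high-pass filtering and intensity normalisation act against drift, and the task signal is a tapping-versus-rest contrast within each run. These measures reduce the time effect; none makes it zero by design.

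Fourth, the Introduction and Discussion allow that subsensory stimulation may itself be active. A change shared by both arms would cancel in the between-arm contrast. This stands as a limit on what that contrast estimates, and is a reason to keep the within-group maps. It does not make a pre-to-post change attributable to stimulation.

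**Conclusion.** The point holds as a wrong inference attached to a stated test, for one secondary imaging outcome. The one-sample test addresses change between scans and cannot by itself verify an effect of stimulation.

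Its size is illustrative. The range of 23% to 35% against 5% rests on an assumed shared time effect of 0.5 SD, 8 to 12 imaged patients per group, and a region-level test without correction. That test is not the plan's cluster procedure. The single-voxel figures (1.8% to 4.4% instead of 0.1%) use the plan's cluster-forming threshold but not its cluster correction.

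A reader might also infer that the trial's main conclusion is at risk. It is not: the JTT analysis and the other secondary outcomes are modelled with intervention and phase factors.

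**What to change.** In the fMRI paragraph of Statistical Analysis:

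1. State that an effect of suprasensory relative to subsensory stimulation on BOLD is judged from the between-arm contrast of pre-to-post change within each phase, in the planned third-level mixed-effects model.
2. State that the difference between phases is judged from the intervention-by-phase contrast, which is nearest to the imaging hypothesis in the Introduction and matches the factors used for the other outcomes.
3. Keep the one-sample maps as descriptive within-group change, and delete the clause saying that they verify effects of stimulation.

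The cost is wording and contrast specification; no new data or procedures are needed. There are two downsides. With equal groups and equal SD, the standard error of the between-arm contrast is √2 ≈ 1.4 times that of a single group's mean change, and that of the interaction is √4 = 2 times, so nominal power is lower. And because subsensory stimulation may be active, these contrasts estimate a difference between two intensities; a change shared by both arms can be described but not attributed to stimulation.
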